CARE-clinical study participants who become pregnant will be discontinued from the study and referred for follow-up per standard of care at the clinic. Any pregnancies to Annovera users will be followed until outcome (i.e., delivery or termination of pregnancy (spontaneous or induced)).

A CARE-clinical study participant will be considered lost to follow-up if she is repeatedly unresponsive to a minimum of three attempted contacts, each on different days, using various methods of communication (e.g., cell phone, home visit, email) for completion of study appointments.

At End of Study visits, Annovera-using CARE-clinical participants will be asked to return their ring for discoloration assessment. A subset of rings will be assayed for residual drug levels (segesterone acetate and ethinyl estradiol).

CARE-qualitative
: Serial cross-sectional IDIs will be conducted with women using or who have discontinued using Annovera at 4, 24 and 52 weeks following method initiation. Interviews will be conducted in-person or over the phone (as per participant’s preference) using a guide. We anticipate that the process of obtaining consent and conducting the interview will take approximately 1 – 1.5 hours.

Women in the OCs/DMPA arm will be interviewed at 4 to 8 weeks following method initiation and will be taken through similar consenting and interview procedures as Annovera users by CARE-qualitative study staff. Male partners of Annovera users will, on the other hand, be interviewed between 12 to 24 weeks following their female partner’s initiation of Annovera. Study staff will take these men through similar consenting and interview procedures as done with women in CARE-qualitative. Women participating in the interviews (in the Annovera or OCs/DMPA arm) at any of the time points and male partners of Annovera users will be compensated at the equivalent of approximately US $5-10 USD (with variation by country) for out-of-pocket expenses (e.g., traveling to and from the study site, their time and inconveniences as a result of participation).

Interviews with health care providers providing Annovera will be conducted when nearly all women continuing to use Annovera have completed the full 13 cycles. Interviews with healthcare providers will be in-person. Unlike other groups of CARE-qualitative participants, health care providers will not receive compensation for participating in the qualitative interviews.

*2.4.6 Study monitoring*

CARE-clinical study monitoring visits will consist of a site initiation visit, periodic monitoring visits, and a site close-out visit. During routine monitoring visits, the monitor will review study documents to verify compliance with the protocol and will review the source documents to confirm the accuracy of the data recorded on the case report forms (CRFs). We established a Data Monitoring Committee (DMC) consisting of three experts with expertise in contraception, epidemiology, and conduct of clinical trials, and who have no financial, scientific, or other conflict of interest with this study. The DMC (charter available on request) will review data approximately every six months, or on an
*ad hoc* basis should unanticipated problems arise. They may provide recommendations about study termination or other modifications to the study.

For CARE-qualitative, participants may be contacted by the study sponsor to determine if they gave informed consent to participate in the research.

*2.4.7 Safety monitoring and adverse event reporting*

The Site PI or designee will monitor and record adverse events (AEs) and serious adverse events (SAEs) for Annovera and non-Annovera users throughout CARE-clinical. AEs and SAEs will be recorded in the appropriate case report forms (CRFs) for inclusion in the study database, with the Site PI or designee determining relatedness, severity, and seriousness. Participants who become pregnant will be terminated from the study and referred for antenatal services. The sites will make every effort to follow-up on all pregnancy outcomes and document in study CRFs.

Annovera and non-Annovera users will be instructed to contact the study site staff to report any AEs and SAEs they experience. At each in-person and remote study appointment, Annovera users will be asked about their general health (how they have been feeling) since their previous appointment. As needed, Annovera users will be examined if symptomatic during an in-person visit or be asked to come to the study site if the appointment is remote.

All SAEs and AEs that lead to study discontinuation will be reported to the relevant IRBs/ethics committees and drug regulatory bodies consistent with applicable regulations, the DMC, and as relevant, the Annovera license holders (in accordance with the approved safety data exchange agreements). AEs and other clinical events will be managed appropriately, in the facility that provided Annovera or by referral to a higher-level facility, if necessary.

Social harms of study participation may include negative consequences related to stigma, discrimination, confidentiality breaches, and psychological distress. Participants will be asked about social harms at study appointments and will be referred to counseling and other support services as needed. Social harm events will be recorded and reported to the relevant IRBs/ethics committees, as applicable. Physical harm related to study participation will be reported as a social harm and any resulting medical adverse consequences (e.g., pain, bruising) will be reported as an AE.

If AEs or social harms are identified during CARE-qualitative, the qualitative team will inform the clinical team as it could be that the participant might not have reported the AEs or social harms to the clinical team.

*2.4.8 Confidentiality*

We will make every effort to ensure the privacy and confidentiality of data collected from all participants screened and enrolled in the clinical or qualitative components of the CARE study. In-person interviews will be conducted in private locations, and telephonic interviews will occur in the location of the participant’s choosing after confirming with the participant that the environment ensured privacy. Access to identifiable information in the research data will be limited to research staff only. Participants’ identifiable study information will not be released without their written permission, except as necessary for review, monitoring, and/or auditing by representatives of the Population Council and its monitors, study staff and/or their representatives, national health ministries, site IRBs, and regulatory authorities. All information disclosed in reports, presentations, or publications will be anonymous. Any breaches in confidentiality will be reported to the relevant IRBs/ethics committees and regulatory authorities.

In CARE-clinical, consented participants will be assigned a unique Participant Identification (PID) Number; no names or other identifying information will be entered into REDCap. All data collected will be recorded using PIDs; no names or other identifying information will appear on any clinical forms, documents, specimens, or any other materials. Study staff will maintain a participant identifier log that includes a list of PIDs with associated names and contact information in a secure location with limited access. All identifiable information will be destroyed after the retention periods prescribed by local regulatory requirements. In CARE-qualitative, all collected data will be treated confidentially and participant names will not appear on the interview transcripts. Rather, pseudonyms will be used to identify participants and transcripts will be identified using PIDs generated by the CARE-clinical component. All data will be kept separately from any identifying information that might be captured in the consent forms. Transcripts will be anonymized and archived in a password-protected computer, and audio transcripts will be erased after the study report is finalized.

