^ A single ring provides one full year (thirteen 28-day cycles) of pregnancy prevention, remains under the user’s control (i.e., can be stopped without consulting a healthcare provider), and does not require daily user action. The ring is inserted vaginally by the user for a 21-day interval, followed by a 7-day ring free interval, and can then be reinserted for a subsequent use cycle. In clinical trials, the typical use Pearl Index pregnancy rate was approximately 3%.
^
16
^ Annovera does not require refrigeration and may reduce the burden on some health care and supply chain systems as compared with provider-dependent methods (IUDs, implants) since it is procedure-free, and can provide a longer duration of protection (one year) than some other self-administered products (e.g., oral contraceptives, Sayana
^®^ Press). Two Phase III trials on Annovera enrolled over 2,300 participants from the United States, Europe, Australia, Brazil, Chile, and the Dominican Republic, but did not include sites in Africa.

Contraceptive vaginal rings can deliver one or more drugs into the vaginal environment. These drugs can act locally or systemically, with steady release over a period of time for non-daily continuous protection, potentially fewer side effects, and less frequent administration requirements as compared with oral routes.
^
17
^ They have emerged as a prominent delivery formulation for development of products targeting an array of indications, such as contraception (e.g., Annovera, NuvaRing), HIV prevention (e.g., Dapivirine vaginal ring), menopause management (e.g., Estring, Femring, Fertiring), and in the ongoing development of multipurpose prevention technologies to simultaneously prevent unintended pregnancy, HIV and/or other sexually transmitted infections (STIs).
^
18
^

Despite the potential advantages of contraceptive vaginal rings in LMICs, some studies have prompted skepticism about the acceptability of vaginal rings in these contexts. In two studies asking potential users about their
*hypothetical* willingness to try various delivery forms, rings did not perform as favorably as other forms.
^
19,
20
^ A qualitative data review suggested that women may have initial concerns about using vaginal rings (e.g., related to insertion or removal, cleanliness, or discomfort), but that these concerns are typically overcome with time during actual ring use.
^
21

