**CARE-clinical **	All female participants must meet the following criteria to be eligible for inclusion: A. Ages 18 through 24 (Zimbabwe) and 18 through 45 (Kenya) years old (inclusive) at screening, verified per site-specific SOPs B. Fluent in spoken Shona (Zimbabwe) or Swahili (Kenya) and/or English C. At risk for pregnancy (post-menarche, no prior sterilization, hysterectomy, oophorectomy, or menopause, per self-report) D. Contraceptive intentions: a. for potential Annovera users, desiring to initiate a new contraceptive method or change from one currently being used; or b. for non-Annovera users, has initiated or changed to OC or DMPA use at enrollment E. At least 12 weeks since last DMPA injection (per review of health record) if ever previously used DMPA F. Sexually active, defined as having had penile-vaginal intercourse with a man within the three months before screening G. Not pregnant at screening or enrollment (per negative pregnancy test) H. Not trying to become pregnant or intending to become pregnant within the next year I. No plans to move away from the study site in next 12 months J. Able and willing to provide informed consent K. Able and willing to provide adequate locator information L. In the opinion of the Site PI or designee, able and willing to comply with the protocol and all study procedures	Individuals who meet any of the following criteria (per self-report except where indicated) will be excluded from the study: A. BMI>29 (per exam at screening) B. Known hypersensitivity to or prior complications with estrogens, progestins, silicone or any of the other components of Annovera C. Not eligible for combined hormonal contraception; this includes an assessment of the following: a. Breastfeeding b. Less than 6 weeks (≤42 days) postpartum c. For women 35 and older, currently smokes cigarettes d. History of deep vein thrombosis or pulmonary embolism e. Prolonged immobilization or anticipating major surgery in the next year f. Thrombogenic valvular or thrombogenic rhythm diseases of the heart g. Inherited or acquired hyper-coagulopathies h. Current or history of cerebrovascular disease, coronary artery disease, or ischemic heart disease i. Uncontrolled hypertension or hypertension with vascular disease (self-report and clinic assessment) j. Systemic lupus erythematosus with positive or unknown antiphospholipid antibodies k. Migraines with aura l. For women over 35 years old, migraines without aura (applicable to Kenya) m. Current breast cancer or within 5 years of past breast cancer n. Diabetes for > 20 years and/or with nephropathy, retinopathy or neuropathy o. Symptomatic gall bladder disease p. Liver tumor, acute hepatitis or severe cirrhosis q. Undiagnosed abnormal vaginal bleeding r. Known condition where steroid hormones are contraindicated D. Use of medications that are contraindicated or believed to have a drug-drug interaction with Annovera E. Current abnormal vaginal discharge, genital tract lesions, or active pelvic infections (for woman in whom the clinician suspects a genitourinary tract infection, treatment should be offered and the woman can enroll following resolution of symptoms) F. History of genital tract surgery (including cervical polypectomy, dilatation and curettage, hysteroscopy, or laparoscopy) in the three months prior to the screening visit G. History of toxic shock syndrome H. Recurrent vulvovaginal candidiasis (defined as more than 3 episodes in the preceding year) I. Current use of vaginal rings (such as Dapivirine ring) or any other instance, as per clinician judgement, where using Annovera along with other vaginally inserted products is not advised J. Any other condition the clinician feels would jeopardize the health and well-being of the participant K. Previous enrollment in the trial as either an Annovera user or non-user

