1], participants may use other medications during the study, and these will be recorded in case report forms. Use of items such as tampons, menstrual cups, and condoms are also permitted. Individuals who pass eligibility screening will receive the equivalent of approximately $10 USD to compensate them for their time and will be enrolled into CARE-clinical. At any point in time, enrolled participants may discontinue use of their contraceptive method (and thus their participation in CARE-clinical) but may not change the arm into which they were enrolled.

**Table 2. T2:** CARE-clinical schedule of enrollment, interventions, and assessments.

	Appointment 1	Appointments 2-5	Appointment 6
	In-person Screening and Enrollment Appointment	Remote Appointments at Weeks 4, 12, 24, & 36 of method use	In-person End of Study Appointment or at discontinuation before 13 cycles of use
Procedure	ANNOVERA USERS: Screening & enrollment done on same day or enrollment procedures done within 30 days of screening visit	±1 week for Appointment 2±2 weeks for Appointment 3-5	Weeks 50-52 or at early discontinuation
Informed consent	X		
Assign participant study identification number (PID)	X		
Record/confirm locator information	X ^ a ^	X	X
Socio-demographics	X		
Medical history and menstrual history	X		
Review/record concomitant medications	X ^ a ^	X	X
Height	X		
Weight and BMI calculation	X ^ a ^		
Blood pressure	X ^ a ^		A
Pregnancy test	X ^ a ^		X
Pelvic examination and/or targeted physical examination if clinically indicated	[A]		[A]
Confirm eligibility	X ^ a ^		
Questionnaire	X ^ b ^	X	X
Protocol adherence & HIV/STI risk reduction counseling	X ^ b ^	X	X
Provide study product/participant insert in clinic	A ^ b ^		
Enquire about adverse events		A	A
Collect used Annovera rings			A

A: Annovera users only.

[A]: To be done for Annovera users only if clinically indicated.

^a^
If enrollment appointment is not on the same day as the screening appointment, procedure is to be repeated during the enrollment appointment.

^b^
Enrollment appointment procedure; to be done following confirmation of eligibility.

Enrollment procedures are slightly different by arm (

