Figure 1). Women who express interest in trying Annovera after contraceptive counseling will be informed that this is only possible for those who enroll in CARE-clinical, since Annovera is not registered in their country. For Annovera-interested women willing to hear more about the study, staff will provide this information, obtain consent from willing individuals, and screen for eligibility. If an Annovera-interested woman is not interested in or eligible for CARE-clinical study participation, clinic staff will counsel her on other available contraceptive options. Study staff will explain to consented, eligible individuals how to use Annovera, provide the Annovera ring and a carrying case, have the participant insert Annovera, assess for discomfort, and enroll her into CARE-clinical. Participants contraindicated for Annovera use due to vaginal conditions identified during ring insertion and who are withdrawn from the study will be replaced. Participants eligible for Annovera can be enrolled within 30 days of the screening visit, but if more than 30 days elapse between screening and enrollment, screening procedures will be repeated. This will occur only once; if a potential participant does not enroll after the second screening visit attempt, she will be excluded from participation.

In contrast, participation in the CARE study is not required for women who wish to try OCs or DMPA, methods which have long been available in these study clinics. To minimize disruption to clinic flow, women who choose to try OCs or DMPA and are medically eligible will be provided their chosen method prior to being presented with information about the study. Only a subset of women who choose to try OCs or DMPA will be invited to learn more about the CARE study, and, if interested, will undergo informed consent and screening (
Table 2).

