^ We will also assay approximately 50-60 returned rings for residual drug levels (segesterone acetate and ethinyl estradiol) from participants who discontinued at various timepoints. Specifically, we will aim to assay rings from approximately 6 participants (3 per site) discontinuing by each of weeks 4, 12, 24, and 36 and from approximately 30 participants (approximately 15 per site) completing the study (a total of 50-60 assayed rings out of the expected 200 used in the study). We will aim for the number of rings assayed at each time point to be similar across both study sites. We will compare residual drug (NES, EE) content of these rings against self-reported days of ring use.

All enrolled participants will be included in all analyses where they contributed data. Select analyses will also be done for the following subgroups: country (Kenya, Zimbabwe), age group (18-24, 25-35, 36-49). Missing data will be treated as missing and not imputed. A statistical analysis plan, to be completed and approved prior to data lock, will provide further detail on analysis specifications.

For CARE-qualitative, we will employ a thematic content analysis approach. This will entail coding the data, developing a list of emerging themes, categorizing themes within a hierarchical framework of main and sub-themes, looking for patterns and associations between themes, and comparing within and between participant groups. CARE-qualitative study investigators will work with two coders (per country) to develop a codebook based on the initial interviews. The coders will then use the codebook to code the remaining transcripts. Any disagreements in coding of transcripts between the two coders will be resolved through discussions between the study investigators and the coders. Insights generated from the qualitative data will elucidate some of the patterns observed in the clinical data, for example, on factors that could explain those patterns.

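### Section 2.4.4 gives two different enrolment points for the Annovera arm; if enrolment follows ring insertion, non-medical first-insertion failures drop out of the continuation result

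*Protocol article*

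**What the plan says.** Section 2.4.4 (Screening and enrollment) describes enrolment into the Annovera arm in more than one way.

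- **Arm-specific narrative.** Once a woman is consented and eligible, staff explain and provide the ring, then "have the participant insert Annovera, assess for discomfort, and enroll her into CARE-clinical". Enrolment is the last step.
- **General narrative, earlier in the section.** Women who clear eligibility screening are compensated and enrolled. Insertion is not a condition.
- **Table 2.** Product provision with in-clinic insertion is an Annovera-only row carrying footnote b: "Enrollment appointment procedure; to be done following confirmation of eligibility".
- **Replacement.** "Participants contraindicated for Annovera use due to vaginal conditions identified during ring insertion and who are withdrawn from the study will be replaced". Nothing is said about a woman who cannot insert the ring or declines it for a non-medical reason.

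OC/DMPA women who are medically eligible "will be provided their chosen method prior to being presented with information about the study". Consent and screening follow. Criterion D.b in Table 1 requires that such a woman "has initiated or changed to OC or DMPA use at enrollment".

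On analysis, section 2.6.3 states: "All enrolled participants will be included in all analyses where they contributed data". Section 2.4.5 times the follow-up calls from the date of enrolment. Table 3 makes continuation at 4, 12, 24, 36 and 52 weeks, compared between arms, a primary objective.

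**The concern.** The moment of enrolment decides who is in the denominator of the continuation curve. If the insert-then-enrol order is followed, a woman who is handed the ring and gives up at the first attempt leaves no trace in that curve. A woman who takes pills home and rejects them at first use is already enrolled and counts as a discontinuer.

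The omitted event is relevant to this study's question. The Introduction notes that "women may have initial concerns about using vaginal rings (e.g., related to insertion or removal, cleanliness, or discomfort", among other things. An acceptability study that does not count failures at this step would describe the ring among women who have already got past it.

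The loss would also reach other results. Reasons for discontinuation would omit these women, and Table 1 bars anyone not enrolled in CARE-clinical from the women's interviews, so the qualitative component could not recover them.

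**Working it through.** **1. The passages side by side**

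| Step | Annovera, arm-specific text | Annovera, general text | OC/DMPA |
|---|---|---|---|
| Consent and eligibility | before ring provision | before enrolment | after method provision |
| Method provided | before enrolment | not placed | before study information |
| Observed first use and discomfort check | before enrolment | not mentioned | none |
| Enrolment | after insertion and check | on passing screening | after consent and screening |

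Table 2 fits either Annovera column: it places insertion after eligibility is confirmed, but does not say whether the woman already counts as enrolled. The replacement sentence refers to women withdrawn from the study, which fits women already in it. The documents do not settle the question.

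**2. The plan's precision figure**

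Section 2.7 gives a maximum standard error of 7% with 200 women per group. At p = 0.5, SE = √(0.25/200) = 3.5%, and 1.96 × 3.54% = 6.9%. The stated 7% is therefore the 95% half-width rather than the standard error. That is a separate matter; 6.9 points is used here only as a yardstick.

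**3. Size of the overstatement**

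Inputs, both assumed because the documents give neither:
- c = continuation among enrolled Annovera women at 52 weeks;
- r = share of women given a ring who fail or decline at first insertion for non-medical reasons.

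If those women count as day-0 discontinuations, continuation among all women given a ring is c × (1 − r). The enrolled-only figure is too high by c × r.

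| r | c × (1 − r), c = 60% | Overstatement | Rings dispensed to reach 200 enrolled, 200/(1 − r), rounded up |
|---|---|---|---|
| 2% | 58.8% | 1.2 points | 205 |
| 5% | 57.0% | 3.0 points | 211 |
| 10% | 54.0% | 6.0 points | 223 |

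Over c = 50% to 80% and r = 1% to 10%, the overstatement runs from 0.50 × 0.01 = 0.5 points to 0.80 × 0.10 = 8.0 points. The factor (1 − r) applies at every time point, so the absolute gap is largest early, while continuation is highest.

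**4. Effect on the comparison between arms**

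Suppose continuation counted from method provision is 60% in both arms. The enrolled-only ring figure is then 0.60/(1 − r) = 61.2%, 63.2% and 66.7% for r = 2%, 5% and 10%. With 200 per arm, a nominal two-sided 5% comparison of two proportions would favour the ring in about 4%, 10% and 28% of trials, against 2.5% with no bias. The plan sets no formal hypothesis, so this is illustrative.

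**5. Satisfaction**

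Section 2.6.3 takes satisfaction from the week 12 and week 52 questionnaires. Section 2.4.5 discontinues from the study anyone who stops her method, and section 2.6.3 does not impute. A day-0 stopper gives neither response whether or not she was enrolled.

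**The case against.** A reader might infer that the discomfort check is a tolerability run-in and that women reporting discomfort are barred from enrolment. The documents do not say so. No Table 1 criterion mentions discomfort or inability to insert, and the general enrolment sentence and Table 2 can be read as enrolling on eligibility, with insertion as one enrolment procedure. That stands. The exclusion follows from the order of steps in one sentence, so the point is conditional on that order being followed.

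A reader might also take the replacement sentence as evidence of the same selection. It covers only women with a vaginal contraindication found at insertion, which is medical ineligibility, and does not support the point.

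Both arms are partly conditioned on having started the method: a woman who chooses DMPA but does not take the injection never enters either. That also stands. What differs is the observed first use and discomfort check, which only the ring arm has before enrolment.

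The Introduction also reports that initial concerns usually fade with use, and cites a review in which few women worried about vaginal insertion. So r may be small, and nothing in the documents supports the upper end of the assumed range.

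Finally, the article condenses a longer protocol, Figure 1 is not shown, and an analysis plan is to follow. But the article states two enrolment points, which is an inconsistency rather than an omitted detail. An analysis plan also cannot recover a discontinuation questionnaire that was never administered.

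**Conclusion.** The point holds in conditional form. Section 2.4.4 does not fix one enrolment moment for the Annovera arm. Under its arm-specific order, non-medical failures and refusals at first insertion are left out of the enrolled-only continuation analysis, with no equivalent step in the OC/DMPA arm. The effect can only favour the ring on a primary endpoint. It equals c × r: 1.2 to 6.0 points at c = 60% and r = 2% to 10%, below the 6.9-point half-width in each of these cases, but not reduced by enrolling more women. Both c and r are assumptions, and the plan as described gives no means of measuring r.

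It would be tempting to say that satisfaction is inflated as well. The documents do not support that: the week 12 and 52 endpoint would miss a day-0 stopper in any case. Continuation and the reasons for discontinuation carry the point.

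This is an inexpensive correction worth making, not a flaw that invalidates the comparison.

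**What to change.** 1. Reconcile the two enrolment statements in section 2.4.4, and Table 2 with them. Set enrolment and time zero for the Annovera arm at ring dispensing, after eligibility is confirmed and before the insertion attempt. This parallels method provision in the OC/DMPA arm.
2. Count a non-medical insertion failure or refusal as a discontinuation on day 0 in the Kaplan-Meier analysis and in the reasons for discontinuation, using the existing early discontinuation questionnaire.
3. Keep exclusion and replacement, as now written, only for women found medically contraindicated at insertion.
4. Report the numbers of women given a ring, not inserting it, and replaced.
5. Table 4 shows recruitment under way. For women already seen, recover these counts where possible from the ring-dispensing forms (section 2.6.1) and the study numbers assigned at consent.

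The cost is a few more end-of-study procedures and early-termination surveys, and some extra early discontinuations in the Annovera arm. Those women take up Annovera places and, because OC/DMPA enrolment is capped at Annovera enrolment, also open comparator places. The week 12 and 52 satisfaction endpoint needs no change.
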